## Abstract

**Background:**

Proton pump inhibitor (PPI) is effective for the treatment of nonerosive gastroesophageal reflux (NERD), but long-term use of PPI is prone to have complications and recurrence after withdrawal. Traditional Chinese medicine (TCM) can relieve the symptoms of reflux and improve the quality of life. The purpose of this study is to evaluate the safety and efficacy of Hewei Jiangni recipe (HWJNR) in the treatment of NERD with cold-heat complex syndrome, and clarify the mechanism of HWJNR on NERD based on the correlation analysis of intestinal flora and metabolites.

**Methods:**

This is a single-center, randomized controlled, double-blind, placebo-controlled clinical trial in which 72 eligible participants with NERD and TCM syndrome of intermingled heat and cold will be randomly allocated in the ratio of 1:1 to two groups: TCM group and western medicine group. The TCM group will receive HWJNR with omeprazole enteric-coated tablets placebo, while the western medicine group will receive omeprazole enteric-coated tablets with HWJNR placebo. Each group will be treated for 8 weeks. The primary outcome is the score of gastroesophageal reflux disease (GERD) health-related quality of life questionnaire (GERD-Q). Secondary outcomes include SF-36 quality of life scale (SF-36), patient-reported outcomes (PRO) self-rating scale score, syndrome score of TCM, and adverse events. Mechanistic outcome is the correlation analysis of intestinal flora and metabolites from healthy individuals and NERD participants before and after the treatment respectively.

**Discussion:**

The goal of this trial is to investigate the efficacy and safety of HWJNR in the treatment of NERD with cold-heat complex syndrome, and to study the composition structure and metabolite expression profile of intestinal flora in patients with NERD through 16SrRNA sequencing and metabolomic correlation analysis of fecal flora, which makes us identify the dominant links of treatment and reveal the potential mechanism of HWJNR.

ChiCTR2000041225. Registered on 22 December 2020

## Administrative information

Note: the numbers in curly brackets in this protocol refer to Standard Protocol Items: Recommendations for Interventional Trials (SPIRIT) checklist item numbers. The order of the items has been modified to group similar items (http://www.equator-network.org/reporting-guidelines/spirit-2013-statement-defining-standard-protocol-items-for-clinical-trials/).

## Introduction

### Background {6-7}

Nonerosive gastroesophageal reflux (NERD) refers to the reflux disease with typical of gastroesophageal reflux symptoms and no mucosal injury under endoscope, also known as endoscopic negative reflux disease [1]. The incidence of gastroesophageal reflux disease (GERD) is increasing yearly based on the epidemiological investigation [2], which has a great impact on the quality of life. The incidence of NERD accounts for about 70% of GERD [3]. Therefore, the effective management of NERD is critical to human health.

Proton pump inhibitor (PPI) is the first-line drug for the treatment of reflux disease [4]. However, long-term use of PPI may lead to the deterioration of nocturnal symptoms and complications, including kidney injury, electrolyte abnormalities, and adrenal diseases [5–7]. The efficacy of PPI in the treatment of NERD is relatively rare compared with erosive esophagitis. Studies have shown that there is a tendency to relapse after drug withdrawal [8]. Due to repeated attacks and side effects of long-term acid suppression, NERD has increasingly become an important and thorny problem in the digestive system.

Vonoprazan, a potassium-competitive acid blocker (P-CAB), is a new type of medicine for the treatment of GERD launched in Japan. P-CABs are stable in acidic environments and exert more potent and prolonged acid-inhibitory effects than PPIs [9]. According to a systematic review, vonoprazan may have a better maintenance effect on GERD compared to PPI, but its precise function is not completely clear for NERD [10]. PPIs effect on acid reflux, but not the main underlying mechanism for GERD (transient lower esophageal sphincter relaxation, TLESR) [11]. Karim et al. believe that transoral incisionless fundoplication (TIF) is more effective than PPI therapy in eliminating troublesome regurgitation and extraesophageal symptoms of GERD [12]. A UK collaborative randomized trial showed that at least up to 12 months after laparoscopic fundoplication, the surgery significantly increased measures of health status in patients with GERD [13]. Surgical treatments have many advantages, but are prone to complications, especially esophageal perforation, which may outweigh any potential risk of long-term use of PPI. Surgical treatment may also face the problems of short duration of treatment and easy recurrence [14, 15].

From the perspective of traditional Chinese medicine (TCM), the stomach belongs to dryness and Yang soil, and majority of them belong to excess and heat, while the spleen belongs to dampness and Yin soil, and most of them belongs to deficiency and cold. According to the clinical observation and research of TCM syndromes, more and more patients with NERD are characterized by mixed syndrome of intermingled heat and cold. This is inseparable from the changes in people’s living standards and dietary structure in modern society. They not only suffer from acid reflux, heartburn, dry mouth, bitterness, and other syndromes of excess heat, but also syndrome of deficiency cold, such as aversion to cold and loose stools. The main features of cold-heat complex syndrome are as follows: (1) burning discomfort behind the sternum or epigastric part; (2) acid regurgitation or vomiting clear water; (3) dull pain in the epigastrium, like warming and pressing. The general principle of TCM treatment is pungent dispersing and bitter descending, harmonizing stomach, and descending adverse qi [16].

Hewei Jiangni recipe (HWJNR) was created by [name] of Dongfang Hospital, Beijing University of Chinese Medicine on the basis of inheriting “Tongjiang theory” in the treatment of spleen and stomach diseases. Table 1 lists the detailed formula. This prescription was based on the in-hospital preparation (“Hejiang capsule” approval number: Beijing Pharmaceutical Z20160002) of Dongfang Hospital to treat NERD patients with cold-heat complex syndrome specifically. Our research group conducted *an observational study* in 2002, which showed that HWJNR could reduce heartburn, acid regurgitation, and other clinical symptoms. The recurrence after 12 weeks withdrawal was significantly less than that in western medicine group. At the same time, studies in mechanism have obtained good progress [17, 18].

**Table 1 Tab1:** Formula of HWJNR

Pinyin name	Latin name	Family name
Huangqin	Radix Scutellariae	Labiatae
Huanglian	Coptidis Rhizoma	Ranunculaceae
Qingbanxia	Pinelliae Rhizoma	Araceae
Ganjiang	Zingiber officinale Rosc.	Zingiberaceae
Zhebeimu	Fritillaria thunbergii Mip.	Liliaceae
Pugongying	Taraxacum mongolicum Hand.-Mazz.	Compositae
Longdancao	Gentianae Radix et Rhizoma	Gentianaceae
Zhishi	Citrus aurantium L.	Rutaceae
Quangualou	Trichosanthis Fructus	Cucurbitaceae
Zhigancao	Glycyrrhiza uralensis Fisch.	Leguminosae

Through the single-center, randomized, double-blinded, placebo-controlled clinical research, this trial aims to evaluate the efficacy and safety of HWJNR in patients with NERD (cold-heat complex syndrome). In addition, this trial intends to reveal the underlying pathogenesis by observing the effects of changes in intestinal bacteriocyte structure on metabolic ideotypes and functional metabolic small molecules.

## Methods/design

### Study design and setting {8-9}

This is a single-center, double-blinded, placebo-controlled, randomized controlled trial (RCT), which will be conducted in Dongfang Hospital, Beijing University of Chinese Medicine. The study is conducted in accordance with the Declaration of Helsinki (Edinburgh 2000 version). The final protocol (Version 2.0, 11 November 2020) of this trial has been approved by Ethical Committee of Dongfang Hospital, Beijing University of Chinese Medicine (Version number: JDF-IRB-2020033602). In addition, this trial has been registered in the Chinese Clinical Trial Registry (No. ChiCTR2000041225, registered on 22 December 2020).

We aim to enroll 72 patients with NERD over a 2-year period (Date from November 2020 to December 2022) from the department of gastroenterology in Dongfang Hospital, Beijing University of Chinese Medicine. Eligible patients will be randomized at a ratio of 1:1 to either TCM group (HWJNR with omeprazole enteric-coated tablets placebo) or western medicine group (omeprazole enteric-coated tablets with HWJNR placebo) for 8 weeks treatment. At the end of this trial, the primary outcome (GERD-Q) and the secondary outcome (SF-36, PRO, syndrome score of TCM) will be evaluated. We will obtain peripheral venous blood, urine, and stool from NERD patients before and after treatment. This study involves 3 site visits (week 0, week 4, and week 8) and 10 call visits (weekly call during the treatment period and follow-up at month 1 and month 3). The process of the study is schematically shown in Fig. 1. And we will additionally recruit 10 healthy controls.

**Fig. 1 Fig1:**
[figure not shown]
Schematic process of the study

### Participants

We aim to recruit patients who have typical gastroesophageal reflux symptoms (such as acid reflux and heartburn), or who do not have typical gastroesophageal reflux symptoms, but have 24-h impedance-pH monitoring showing that they are related to gastroesophageal reflux. The symptoms above are not less than three months, and the gastroscopy show nonerosive gastroesophageal reflux. The inclusion criteria of TCM refers to the diagnosis of cold-heat complex syndrome in the “consensus on Integrated traditional Chinese and Western Medicine diagnosis and treatment of gastroesophageal reflux Disease” issued by the Digestive Professional Committee of the Chinese Society of Integrated traditional Chinese and Western Medicine in 2017 (Table 2). The inclusion criteria of western medicine is based on the consensus of experts on gastroesophageal reflux disease issued in 2014 (Table 3). And we will also recruit 10 healthy subjects for control.

**Table 2 Tab2:** Diagnostic criteria for cold-heat complex syndrome of NERD

Category	Symptoms or signs
Main symptom	Burning discomfort in the retrosternal or epigastric region. Anti-acid or spitting clear water. Dull pain in the epigastric stomach, like warming, and pressing. Fasting stomachache, relieved by eating.
Minor symptoms	Loss of appetite; Fatigue; Thin stools; Lukewarm hands and feet.
Tongue	Red tongue, White fur
Pulse condition	Weak pulse

**Table 3 Tab3:** Inclusion criteria of NERD

Those who have the typical clinical symptoms of NERD, such as heartburn and reflux, persist or recur for more than 3 months, and the above symptoms have a negative impact on the quality of life of the patients. Those who have atypical or extraesophageal symptoms, such as epigastric pain, abdominal distension, belching, non-cardiogenic chest pain, pharyngitis, cough, asthma, or foreign body sensation in the throat, which persist or recur for more than 3 months, the above symptoms have a negative impact on the patient’s quality of life: mild symptoms ≥ 2 days in a week, or moderate and severe symptoms ≥ 1 days in a week. Reflux diagnostic questionnaire (RDQ) scale symptom score ≥ 12, which is for diagnosis of reflux diseases in the China gastroesophageal reflux Research Cooperation Group. Those who have no esophageal mucosal lesions and Barrett esophageal manifestations by gastroscopy. Tweny-four-hour esophageal impedance-PH monitoring: impedance records showed reflux events. At the same time, symptom association probability (SAP) is used to determine the relationship between symptoms and reflux. If SAP > 95%, symptoms will be considered related to reflux.	

Diagnostic criteria: 1&3&4 or 2&4&5

The main symptom 1 or 2 is necessary. Patients with two main symptoms + either of the other one or two minor symptoms + appropriate tongue and pulse condition can be diagnosed as cold-heat complex syndrome

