### Eligibility criteria {10}

#### Inclusion criteria for subjects

Patients meet the diagnostic criteria of NERD in guide and TCM with cold-heat complex syndrome at the same time.18–65 years old.Those who did not receive similar drugs (PPI, H2 receptor antagonist, gastric mucosal protective agent, etc.) within 2 weeks before the trial.Voluntarily participated in this study and signed the informed consent form (ICF).

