#### Inclusion criteria for healthy subjects

Those who have no typical clinical symptoms of NERD such as acid regurgitation, heartburn, and reflux.The score of GERD-Q scale < 8 points.18–65 years old.Those who voluntarily participate in this study and sign the ICF.

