#### Secondary outcome measurements

Quality of life score: According to the Chinese version of SF-36 health survey [19], the quality of life will be evaluated from 9 dimensions: physical function, physical function, physical pain, general health, vitality, social function, emotional function, and mental health. All the indexes will be recorded at baseline, week 4, and week 8.Patient-reported outcomes (PRO) self-rating scale score: There will be a diary card for patients to fill in every day. The researchers will calculate the PRO self-rating scale score according to the patient’s diary card at baseline, week 4, and week 8.TCM clinical syndrome score: According to the diagnostic criteria of cold-heat complex syndrome, the main and minor symptoms, tongue, and pulse will be graded and scored by using a unified table. All the indexes will be recorded at baseline, week 4, and week 8. According to the referred Guidance Principle of Clinical Study on New Drug of Traditional Chinese Medicine [20], all symptoms will be divided into four grades: none, mild, moderate, and severe, with 0, 2, 4, and 6 points in the main symptoms, and 0, 1, 2, and 3 points in the minor symptoms. In addition, the tongue and pulse will be divided into normal and abnormal grades, with 0 and 2 points.

The clinical efficacy will be evaluated as follows:
Clinical recovery: the symptoms disappeared or syndrome score decreased by ≥ 95% from the baseline.Marked efficacy: the syndrome score decreased by ≥ 70%, but < 95% from the baseline.Effective: the syndrome score decreased by ≥ 30%, but < 70% from the baseline.Ineffective: the symptoms and signs were not significantly improved, or even aggravated, and the syndrome score decreased by < 30% from the baseline.Aggravation: the syndrome score after treatment is higher than that before treatment.

TCM syndrome efficacy rate = (clinical recovery + marked efficacy + efficacy) cases/a total number of cases × 100%.

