### Statistical analysis {20}

Efficacy analysis will be performed based on both FAS and PPS patients. Safety analysis includes all randomized participants who take at least one bag of HWJNR and have data for safety assessment. Comparing the healthy control group with the traditional Chinese medicine group, we will study the composition of the intestinal flora and the expression of metabolites in patients with NERD and the healthy group. And it will also reveal the mechanism of action and advantages of HWJNR in the treatment of NERD patients.

Changes from baseline to post-treatment in GERD-Q, SF-36, PRO, and syndrome score of TCM will be analyzed using analysis of covariance with associated 95% confidence intervals. All the analysis results will be generated by SPSS 25.0 software. Repeated measurement data are expressed by mean ± standard deviation, intra-group comparison is performed by analysis of variance of repeated measurement data, and inter-group comparison is by multivariate analysis of variance (MANOVA). *P* ≤ 0.05 indicates that the difference is statistically significant. Unilateral test will be used in all statistical tests, and the significance level *P* ≤ 0.05. The arithmetic mean, standard deviation, median, minimum, and maximum will be calculated according to the data distribution. Counting data will be used to calculate the number and percentage of cases.

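### The fecal flora and metabolite contrast with healthy controls may partly reflect the TCM syndrome or stool form, because syndrome criteria that include thin stools apply to patients only, yet the contrast is read as a feature of NERD

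*Protocol article*

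**What the plan says.** **Patients.** The protocol article (Inclusion criteria for subjects) requires both conditions: "Patients meet the diagnostic criteria of NERD in guide and TCM with cold-heat complex syndrome at the same time". Table 2 under Participants lists the minor symptoms of the syndrome as "Loss of appetite; Fatigue; Thin stools; Lukewarm hands and feet". The note to the diagnostic tables counts minor symptoms toward the diagnosis: "Patients with two main symptoms + either of the other one or two minor symptoms + appropriate tongue and pulse condition". The Background also names looser stools as typical of the syndrome: "syndrome of deficiency cold, such as aversion to cold and loose stools".

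**Healthy controls.** The first inclusion criterion is "Those who have no typical clinical symptoms of NERD such as acid regurgitation, heartburn, and reflux". The others are a GERD-Q score below 8, age 18 to 65 and consent. The exclusions concern esophageal, organic and serious disease, pregnancy, mental and neurological conditions, and other trials. Neither list mentions stool form, bowel habit or TCM syndrome.

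**Assay and reading.** Biological specimens says that the flora and metabolites are examined in feces. Statistical analysis compares the TCM group with the healthy controls and says "we will study the composition of the intestinal flora and the expression of metabolites in patients with NERD and the healthy group". The mechanistic outcome adds that key strains will be screened and their role in the pathogenesis of NERD explored.

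**Data at hand.** The TCM clinical syndrome score grades each minor symptom at baseline, week 4 and week 8, with "0, 1, 2, and 3 points in the minor symptoms". A thin-stool grade therefore exists for each patient. The text shown schedules no such grade for controls.

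**The concern.** The entry rule selects patients partly on a property of the material that is then sequenced and profiled, and it does not select controls on that property. The design also has no NERD patients without the syndrome and no controls with it. A patient-versus-healthy difference can therefore come from NERD, from the syndrome, or from stool form.

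A taxon or metabolite that merely tracks loose stools could be picked up as differential and carried forward as a candidate in the pathogenesis of NERD. With only 10 controls, a few participants can move the comparison noticeably.

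**Working it through.** The plan states no figure on this point, so there is none to reproduce. The check asks how far the entry rule could raise the share of patients with thin stools, and what that could do to the contrast.

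**Inputs from the protocol article:** 36 patients per arm, 72 in all; 10 healthy controls; four minor symptoms, none of them mandatory.

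**Assumptions, not in the documents:** the prevalence of thin stools, the independence and equal prevalence of the minor symptoms (step 1 only), and a difference of 0.8 SD between thin and formed stool for a feature that has nothing to do with NERD.

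**Step 1. Enrichment.** Let each of the four minor symptoms have prevalence p before selection.
- At least one required: P(thin stools | selected) = p / [1 − (1 − p)^4].
- At least two required: P(thin stools | selected) = p × [1 − (1 − p)^3] / P(at least 2 of 4).

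| p before selection | At least one required | At least two required |
|---|---|---|
| 10% | 29% | 52% |
| 20% | 34% | 54% |
| 30% | 39% | 57% |
| 40% | 46% | 60% |
| 50% | 53% | 64% |

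For p = 10% and at least one required: 0.10 / (1 − 0.9^4) = 0.10 / 0.3439 = 0.29. With a 10% background share, the two readings give roughly 30% and 50% in patients. Those are the scenarios used below.

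**Step 2. Spurious shift.** Shift = 0.8 SD × (share in patients − share in controls).
- 30% v 10%: 0.8 × 0.20 = 0.16 SD
- 50% v 10%: 0.8 × 0.40 = 0.32 SD

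**Step 3. False-positive rate for one such feature.** Two-sample t test, two-sided 5%, with non-centrality = shift / √(1/n1 + 1/10). The square root is 0.357 for 36 patients and 0.337 for 72.

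| Shift | 36 v 10 | 72 v 10 |
|---|---|---|
| 0.16 SD | 7.2% (non-centrality 0.45) | 7.5% (0.47) |
| 0.32 SD | 14.1% (0.90) | 15.5% (0.95) |

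The nominal rate is 5%. The 36 v 10 column matches the contrast named under Statistical analysis, which is the TCM group against healthy controls. The 72 v 10 column would apply if both arms were pooled at baseline.

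**Step 4. What a restricted analysis leaves.** If half the patients have thin stools, 36 × 0.5 = 18 TCM-group patients have grade 0. If 10% of controls do, 9 of 10 remain. For a true NERD difference of 0.8 SD, two-sided power falls from 59% (36 v 10, non-centrality 2.24) to 47% (18 v 9, non-centrality 1.96).

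**The case against.** **This is silence, and the article is condensed.** The article does not say that stool form will be ignored, and covariates for an omics analysis are often left to a fuller document. That stands as far as the covariates go, so no decision to ignore stool form should be inferred. It does not remove the point: the eligibility rules for both groups, and the reading of the contrast as a feature of NERD, are fixed in the article.

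**Enrichment is uncertain.** A reader might infer that the patients as a group have loose stools. The documents do not support this. Thin stools is one of four optional symptoms, and the wording of the rule is unclear enough that a patient might qualify on a further main symptom with no minor one. If one minor symptom suffices and such symptoms are common, enrichment is slight (40% to 46%, or 50% to 53%).

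**The data are not all there.** A reader might infer that the trial already holds what it needs to adjust. The grade is documented for patients only (the schedule in Table 4 is not shown), and it scores a symptom, not the assayed sample.

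**The size could be made to look larger.** The plan announces one-sided tests, and for a 0.32 SD shift a one-sided test in the direction of that shift gives 22% to 24%. In the opposite direction the rate is only about 0.5%. A flora screen has no prespecified direction, so the two-sided figures are the fair ones.

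**The randomized comparison is safe.** A reader might extend the concern to HWJNR versus omeprazole. Both arms enter under the same rule and are randomized, and flora and metabolites are measured at baseline in both, so this asymmetry does not bias that comparison.

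**The wording is partly right already.** The stated aim refers to NERD with cold-heat complex syndrome. Only the mechanistic outcome, the statistical section and part of the Discussion fall back on NERD alone.

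**Conclusion.** The point holds as a modest caveat on an exploratory, non-randomized comparison. Patients are selected on a syndrome for which thin stools can count, controls are not, and the fecal contrast is nevertheless described as a feature of NERD. It may partly reflect the syndrome or stool form.

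Under the assumptions above, the false-positive rate for a stool-dependent feature is about 7% to 14% with 36 v 10 and 8% to 16% with 72 v 10, against 5%. These figures illustrate scale only. They apply only to features that stool form affects, and a smaller stool effect or weaker enrichment brings them back toward 5%. The primary outcome, the safety analysis and the randomized between-arm comparison are unaffected. No analysis of these data can separate NERD from the syndrome, because the two always occur together in the patients and controls are not selected or graded on the syndrome.

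**What to change.** 1. Record the same thin-stool item, graded 0 to 3, in the 10 healthy controls when they give their sample.
2. Report the patient-versus-healthy contrast as planned and, as a sensitivity analysis, restricted to participants with thin-stool grade 0 or adjusted for the grade. Give estimates and confidence intervals for both, and flag features whose estimated difference shrinks markedly.
3. Do not delete a feature because it loses significance in the restricted analysis. With 18 v 9, a true 0.8 SD difference would be missed about half the time (power 47%). If loose stools result from the altered flora, restriction would also remove real signal.
4. Word the conclusion as NERD with cold-heat complex syndrome versus healthy, in the mechanistic outcome, the statistical section and the report.

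**Cost:** one question for 10 people, one extra analysis and a change of wording; patients need no new data. The downside is lower precision in the restricted analysis, with about 18 of 36 TCM-group patients left if half have thin stools.
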